#### E-helpers

The e-helpers will assist in the use of SbS-F mobile phone application and remind participants to log in if they show inactivity. The e-helpers will also identify cases requiring a higher level of care than what SbS-F is designed to deliver. When a high-risk case is identified, the e-helper will encourage the user to contact local supportive services and inform the clinical supervisor. The results of the SbS-F website version feasibility study suggested that a minimal guidance model that included asynchronous on-demand support was sufficient to maintain adherence and retention.

Filipino e-helpers will provide technical and motivational support to OFW users. These e-helpers could be community health workers, graduate students, or upper-level undergraduate students under the supervision of their professor. The e-helpers’ training and guidance will be conducted as a part of a student practicum experience, so students will receive course credit for their participation (Appendix 3). This will be coordinated and supervised by our academic partners at De La Salle University in the Philippines.

E-helper support consists of guiding users through the intervention and supporting them in conducting their own activities. This on-demand guidance will be conducted by the email-like message system (a delay in response) available within the mobile application. This support will be available to users upon their request and users will be allocated to a particular slot and e-helper by the supervisor based on availability and preference. The e-helpers also need to be able to attend weekly supervision sessions with a clinical supervisor. A clinical supervisor will supervise e-helpers and, in emergency situations, provide support, ensure the guidance model was being followed, and troubleshoot any difficulties. Supervision ideally would take place during weekly group meetings, where cases are presented and issues are discussed.

The e-helpers will need to be available for training. Training on digital mental health and scalable psychological interventions will be provided for all e-helpers. This will include a broader orientation to global mental health and the WHO scope of work to address the burden of mental ill health through scalable intervention models. The e-helpers would be also trained on the intervention and how to facilitate/guide the intervention remotely using asynchronous message system and audio call support.

### Sample size

Based on previous behavioral-activation smartphone application RCT study [41], the expected pragmatic total sample size for this pilot study is 53 participants for each group. This sample size target is necessary for a pilot hybrid type study to evaluate the potential challenges for SbS-F implementation in the real-world settings [45]. Estimating the effect size is not an aim of this pilot study because preliminary effectiveness of SbS-F asked in research questions 1 and 2 are exploratory. To achieve this total sample size of 106 participants, 650 participants are targeted for recruitment in anticipation of attrition that is summarized in Fig. 2 of CONSORT flow diagram. From a previous population study with OFWs in Macao [11, 19, 46], it is predicted that 40% of screened participants will be eligible for baseline and 50% of participants during the intervention stage will drop out.

### Recruitment

Participants for SbS-F intervention will be recruited through assistance of a local community partner (CM), for example, on the Caritas Open Day event. Members of our research group will attend the event, together with staff of CM, to explain the intervention program and invite OFWs to participate in the screening process. Together with CM, recruitment will also be conducted at churches by the assistance of the priests who will inform parishioners about the study. Additionally, the research assistants will distribute flyers that contain a link and QR code to the screening survey after the weekly mass. Churches are chosen because the majority of Filipino are Christian/Catholic [47]. For the qualitative methods, purposive sampling technique will be used to select participants with particular characteristics (e.g., by sex and by participants’ involvement during the intervention). The participant numbers of qualitative methods will be determined following the number of participants in trial and established methods for qualitative research [48]. Online recruitment via social media is also an effective strategy used during the feasibility study [26, 49]. Facebook recruitment advertisements and other targeted social media messaging via opinion leaders within the Filipino community will also be used.

### Randomization and blinding

Participants will be randomized by the built-in algorithm in the mobile app with 1:1 ratio to the treatment (SbS-F) and control (ECAU) arms. The algorithm is designed for permuted block randomization where the total number of participants is set prior to the randomization. The algorithm will also randomly choose the length of the block (2, 4, or 6) and the order within a block is also randomly assigned. For illustration, 20 participants can be randomized into this scenario where “T” is for treatment and “C” is for “Control” group: [TCCT], [TTCTCC], [CT], [TC], [CTCT], and [CT]. As a part of the consent process in the screening stage, participants will be informed that this is an intervention study where they might be assigned to different treatment groups. Due to the characteristics and design of this study, blinding of treatment assignment and outcome assessments will not be feasible.

### Participant eligibility

Male or female OFWs will be included if they meet the following criteria: (1) aged 18 or over; (2) understand English and/or Tagalog; (3) holds a valid working visa in Macao; (4) will stay in Macao for at least 6 months more; (5) have a mobile phone; (6) have internet access; and (7) score ≥ 10 on the Patient Health Questionnaire (PHQ-9). OFWs will be excluded from the study if they (1) have suicidal intent based on an item of suicidality screening (“In the past month have you had serious thoughts or a plan to end your life?”); (2) are not physically present in Macao during the study; and (3) are younger than 18 years old.

### Assessments

There will be five measurement time points: (1) screening, (2) baseline, (3) monitoring, (4) endline, and (5) follow-up. A summary of assessment measurements in this study is presented in Table 3 below following standard protocol items for clinical trials (SPIRIT, Additional file 1). Participants in both trial arms will receive compensation for their time and costs associated with required internet use at screening, endline, and follow-up (roughly 6 USD for screening, and 12 USD for endline and follow-up).

**Table 3 Tab3:** Outcomes and time points of measurement following the SPIRIT guidelines

Outcome	Instrument	Screening	Baseline	Monitoring	Endline	Follow-up
Week			1	3-7	8	20
Sociodemographic (age, education level, sex, marital status, occupation, years as OFW, years of worked in Macao, salary, visa status)	Demographic questions	x	x			
Source of getting SbS-F information	Demographic questions	x				
Mental health care service history	Demographic questions	x	x	x	x	x
Intention to stay in Macao	Demographic questions	x	x			
Smartphone ownership	Demographic questions	x	x			
Internet access	Demographic questions	x	x			
Contact details	Demographic questions	x				
Convenient contact times	Demographic questions	x				
Depression symptoms	PHQ-9	x	x	x	x	x
Anxiety symptoms	GAD-7		x		x	x
Wellbeing	WHO-5		x		x	x
“Adoption” (RE-AIM)	Questionnaires Interviews and focus groups	x			x	
“Implementation” (RE-AIM)	Questionnaires Interviews and focus groups				x	
“Maintenance” (RE-AIM)	Questionnaires Interviews and focus groups					x

*Note*. *GAD-7* Generalized Anxiety Disorder-7, *OFW* overseas Filipino worker, *PHQ-9* Patient Health Questionnaire, *RE-AIM* Reach, Efficacy/Effectiveness, Adoption, Implementation, and Maintenance framework, *SbS-F* Step-by-Step program (Filipino version), *WHO-5* WHO-5 Wellbeing Index

#### Demographic information

In the screening, the participants’ sociodemographic and personal information will be administered first by combining open and closed questions. Samples of open questions are participants’ age, years as OFW, and salary. For closed questions, participants will be given options to choose from, for example, education level (elementary / high school / technical school / some college / college degree or higher), intention to stay in Macao at least 6 months more (yes / no), and access to internet on a smartphone (yes / no). In the Baseline session, participants will be asked again about their sociodemographic and personal information to confirm their eligibility.

#### Primary outcome measurement

The primary outcome is self-reported depression symptoms that will be measured with Patient Health Questionnaire-9 (PHQ-9), a self-administered, relatively short and simple depression scale drawn from the full Patient Health Questionnaire [50]. It is designed to measure depressive symptoms according to the DSM-IV criteria [51] and DSM-5 since no significant difference between DSM-IV and DSM-5 for depression diagnosis criteria [52]. Items are rated from 0 (not at all) to 3 (nearly every day) and scores on each item are summed such that the total score ranges from 0 to 27. Higher scores represent greater depressive symptom severity. The Filipino version of PHQ-9 has been validated for use among female migrant domestic workers [9, 11] and showed high reliability (*α* = .93).

#### Secondary outcomes measurements

Two secondary outcomes of intervention preliminary effectiveness are self-reported anxiety symptoms and wellbeing of participants. The anxiety symptoms will be measured with the Generalized Anxiety Disorder-7 (GAD-7), which was originally developed among primary care patients [53]. The GAD-7 has been translated into various languages and adapted to different contexts, has good psychometric properties, and has good sensitivity and specificity to detect anxiety depression [54]. Items are rated from 0 (not at all) to 3 (nearly every day), and scores on each item are summed such that the total score ranges from 0 to 21. Higher scores represent greater anxiety symptom severity. The Filipino version of GAD-7, which will be used in this study, showed good internal consistency (*α* = .80) in studies among Filipino domestic workers [11, 55].

The psychological wellbeing of participants will be measured with the WHO-5 Wellbeing Index (WHO-5) that has non-invasive questions with high sensitivity in capturing positive affect [56, 57]. Items are rated from 0 (none of the time) to 5 (all of the time), and scores on each item are summed; the total score ranges from 0 to 25. Higher scores represent greater sense of wellbeing. A cross-sectional study in Taiwan that used the WHO-5 found that Filipino migrant care workers reported higher psychological wellbeing than caregivers from Vietnam and Indonesia [58]. The WHO-5 has been also used among Filipino older adults and showed good internal consistency (*α* = .88) [59].

#### Implementation measurements

As a hybrid type 1 trial, this study will assess the SbS-F potential implementation by following the RE-AIM framework as presented in Table 1 with a mixed-methods approach. The quantitative data will be sourced from the administrative information (i.e., duration in accessing the SbS-F application) and questionnaires adopted from a previous hybrid trial of interpersonal psychotherapy for prisoners with depression [45].

The Stakeholder Acceptability Survey (SAS) [60] will be used for assessing ease of delivering SbS-F, the perceived helpfulness of SbS-F, level of enthusiasm for SbS-F, and issues related to sustainability. The stakeholders’ attitudes toward evidence-based practice will be assessed with the revised Evidence-Based Practice Attitude Scale (EBPAS-50) [61]. The stakeholders’ attitudes, knowledge, and skills needed to provide high-quality mental health care will be assessed using Competency Assessment Inventory (CAI) [62]. The perceived barriers and facilitators of implementation from the stakeholders’ perspective will be measured with the Dimensions of Organization Readiness—Revised (DOOR-R) survey [63].

The qualitative data will be gathered through semi-structured individual interviews and focus group discussions with the participants and stakeholders (e.g., staff of local community partner and e-helpers). The interviews and focus group discussion guidelines draft can be found in Appendix 4 and will be finalized following completion of SbS-F intervention since this is an iterative process of qualitative enquiry.

### Ethical considerations

#### Ethical and safety considerations

The SbS-F in this study is a non-pharmacological digital mental health intervention. Similar interventions have been found to be safe for treating depression [64, 65]. The protocol of this hybrid trial has been approved by the Research Ethics Committee at the University Macau (SSHRE19-APP074-FSS) on 16/01/2020 and has also be registered publicly (Chinese Clinical Trial Registry, ChiCTR2000034959) on 26/07/2020.

This treatment is unlikely to induce adverse effects but the severity of depression will be monitored regularly using PHQ-9 following self-harm protection protocol for a study among adults with depression [34]. If a participant develops into a high-risk case (i.e., scoring 2 or above on item 9 of the PHQ-9) during the intervention period and endline, an e-helper will refer the participant to local counselling services and be followed-up. Additionally, participants who answer 2 or above on item 9 of the PHQ-9 will receive a pop-up message on their screen explaining that they may need additional mental health support. Participants who are excluded in the screening because of suicidal ideation will also be referred to local counselling services. The e-helpers will also refer the participants deemed as moderate- and high-risk cases to counselling services and report to the e-helper supervisor and research staff.

Participants who show inactivity in several days (i.e., 7 days) will be sent a message and up to three audio call follow-ups. Participants who indicate that they wish to discontinue the intervention will be invited to provide their e-helper with a reason for discontinuation. The answers from this process will be used in implementation evaluation, particularly on barriers for participation. If participants state that the discontinuation is due to intensified distress, appropriate alternative referrals will be discussed with the participants and initiated when necessary.

The intervention also seeks to ensure no participants will experience stigma from participating. The content of the intervention will look like illustrated story within the mobile application and any sensitive or potentially culturally offensive wordings are removed or reworded based on our completed qualitative cultural adaptation [26].

There is no identified risk in the qualitative interviews with participants and stakeholders. However, interviewers will be trained in responding to distress as a result of interview questions. Should distress arise, interviewers will provide participants a list of contacts for counselling services for additional support.

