**Fig. 2 Fig2:**
[figure not shown]
Overview of SbS-F hybrid trial study design following CONSORT diagram

**Table 1 Tab1:** The Reach, Efficacy/Effectiveness, Adoption, Implementation, and Maintenance (RE-AIM) framework

Domain and outcome (example)	Source
**R**each • Participant’s and decliner’s characteristics (e.g., compare sociodemographic information between participant and nonparticipant OFWs; reasons for not participating; the most effective recruitment strategy)	• Administrative data • Open-ended questions in a questionnaire
**E**ffectiveness • Primary outcome (depression severity) • Secondary outcome (anxiety and wellbeing) • Reason for withdrawing	• Questionnaires • Interviews and focus groups
**A**doption • Ineligibility reasons • Barriers and enablers of SbS-F adoption into community partner’s program and recommendations for addressing barriers and maximizing adoption • Community partner’s knowledge and beliefs about the SbS-F program	• Administrative data • Questionnaires • Interviews and focus groups
**I**mplementation • Participants’ adherence to the intervention (e.g., duration in accessing the SbS-F and reasons for missing sessions) • Participants’ perceived benefit from the intervention • Barriers and enablers in implementing the program and modifications needed to maximize the implementation (from participants’ and staff’s perspective) • Relevance of the SbS-F story and techniques in participant’s lives • Time and resources required for supporting the program (e.g., number of e-helpers needed and their total working time; e-helpers’ training, selection, and retention)	• Administrative data • Questionnaires • Interviews and focus groups
**M**aintenance • Attrition rates • The durability of intervention effects on depression • Resources, strategy, and policy needed to integrate and maximize the SbS-F intervention into community partner’s program after the study ended	• Administrative data • Questionnaires • Interviews and focus groups

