3		Session 1: Get started (psychoeducation and trying small and pleasant activities)
4		Session 2: Get active (behavioral activation)
5		Session 3: Beat obstacles (more complex behavioral activation and relaxation)
6		Session 4: Get together (increasing social support)
7		Session 5: Keep it up (relapse prevention).
8	Endline assessment	Endline assessment
20	Follow-up assessment	Follow-up assessment

*Note*. *SbS-F* Step-by-Step program (Filipino version)

On the other side, participants in control group will receive ECAU, which consists of brief psychoeducation on depression and a referral to CM services. This basic depression psychoeducation is formulated based on the information provided during the first session of SbS to assure that the information is same between two groups. A previous study found that online psychoeducation reduced depressive symptoms among adults in Indonesia [15]. In addition, participants will receive information on services provided by CM. There are two CM departments named WelAnser Centre (WC) and Life Hope Hotline (HH) that can be accessed by participants. In WC, there are three social workers with Bachelor of Social Work degree who handle mental health problems of migrant workers with supportive counselling services. These social workers received mental health-related education in their bachelor’s degree and practical mental health care trainings through the Macao Social Welfare Bureau. If the issue is beyond the social worker’s expertise or CM’s scope of service, the client will be referred to another agency. For example, a client who needs medication will be referred to the hospital and accompanied by the social worker as needed.

Due to geographical and time difficulties, not all OFWs can visit the WC to have counselling. Alternatively, they can contact HH for emotional support through phone counselling that is available 24/7. The phone counselling provided by HH is available in Cantonese, Mandarin, and English, with counsellors from a social work or psychology bachelor’s degree background. Moreover, every counsellor at HH has been trained about mental health and crisis intervention. In addition, there is a regular supervisory meeting to discuss any challenges faced by the counsellors. Similar with the counsellors at WC, if the client’s problem is beyond their expertise or CM’s available services, the counsellor will provide client information about other agencies that may be able to assist their needs.

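### Referral with follow-up for a high-risk PHQ-9 item-9 score is promised only up to endline (week 8), but PHQ-9 is collected again at week 20

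*Protocol article*

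**What the plan says.** Ethical and safety considerations defines a high-risk case by a threshold ("i.e., scoring 2 or above on item 9 of the PHQ-9") and attaches a response to it: "during the intervention period and endline, an e-helper will refer the participant to local counselling services and be followed-up".

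Two other sentences in that section carry no time limit. One is an automatic message: "participants who answer 2 or above on item 9 of the PHQ-9 will receive a pop-up message on their screen". The other has e-helpers "refer the participants deemed as moderate- and high-risk cases to counselling services and report to the e-helper supervisor and research staff".

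The schedule is in Assessments: "There will be five measurement time points: (1) screening, (2) baseline, (3) monitoring, (4) endline, and (5) follow-up". Table 3 marks PHQ-9 at all five, with baseline in week 1, monitoring in weeks 3 to 7, endline in week 8 and follow-up in week 20. Table 2 ends with a week-20 row, "Follow-up assessment", in both the control and the intervention column. The late depression measurement has a planned use: Table 1, under Maintenance, lists "The durability of intervention effects on depression".

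**The concern.** The rule that includes follow-up names its own window, and the window stops one PHQ-9 short of the schedule. Staff who read the sentence literally have no stated duty to follow up a participant whose item-9 score is 2 or above at week 20.

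The omission falls at an awkward point. After a high-risk score at week 8, follow-up is promised and a later PHQ-9 is still to come. At week 20 neither is true. Referral without follow-up may also not lead to care in this population. According to Setting and timeline, the public hospital's psychology and psychiatry department opens only on weekdays, when migrant workers are usually at work, and the private fee is 10 times higher. Intervention and control groups adds that not every worker can get to the counselling centre, and that the telephone alternative runs in Cantonese, Mandarin and English, whereas eligibility accepts people who understand only Tagalog. Suicidal intent is an exclusion at screening, asked over the past month, so it does not rule out risk that emerges later.

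What is at stake is participant safety. The treatment comparison is unaffected.

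**Working it through.** The article gives no figure to reproduce. The check sets the safety wording against the PHQ-9 schedule.

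**Inputs**
- Trigger: item 9 scored 2 or above (Ethical and safety considerations).
- Window for referral with follow-up: intervention period and endline (same section).
- PHQ-9 weeks after screening: 1, 3 to 7, 8 and 20 (Table 3).

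**Stated response to the trigger at the two late assessments**

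| Response | Endline, week 8 | Follow-up, week 20 |
|---|---|---|
| Pop-up message | yes | yes, if the untimed sentence applies |
| E-helper referral to counselling | yes | yes, if the untimed sentence applies |
| Report to supervisor and research staff | yes | yes, if the untimed sentence applies |
| Follow-up of the participant | yes | not stated |
| A later scheduled PHQ-9 | yes (week 20) | none |

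On the most generous reading, the difference in the stated response is the follow-up. On a stricter reading, in which the named window governs the whole e-helper response, referral is missing at week 20 as well. Either way the stated response is weaker than at week 8.

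The E-helpers section has one more untimed line: on identifying a high-risk case, the e-helper encourages the user to seek local support and informs the clinical supervisor. It does not promise follow-up either.

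**Timing**
- Last week with stated follow-up: 8. Last PHQ-9: 20. Gap: 20 − 8 = 12 weeks.
- PHQ-9 assessments scheduled after week 20: 0.

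The 12 weeks only place the uncovered assessment. No PHQ-9 is scheduled between weeks 8 and 20, so the gap is one assessment, not 12 weeks of unanswered scores.

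**Is cover at week 20 secured elsewhere in the article?**
- E-helper training and guidance is "conducted as a part of a student practicum experience, so students will receive course credit for their participation". No end date is given, so this shows neither that cover lapses nor that it lasts.
- Appendix 1 starts recruitment in month 7 and marks follow-up and implementation evaluation in months 9 and 10. From week 1 to week 20 is 19 weeks, or 19 × 7 = 133 days; 133 / 30.4 ≈ 4.4 months. Someone whose week 1 falls at the very start of month 7 (6.0 months elapsed) reaches week 20 at 6.0 + 4.4 = 10.4 months elapsed, which is in month 11. The timeline therefore does not show cover at week 20.

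The main conclusion does not depend on either of these two points.

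**The case against.** The strongest reply is that most of the response is already there. High risk is defined once, and the untimed sentences then give a high-risk score at week 20 a pop-up, a referral and a report to the supervisor. Only the follow-up is missing, and its content, duration and responsible person are not specified even at week 8. Reporting to a supervisor is itself a plausible route to follow-up. This stands as a limit on size: it would be wrong to say that there is no response at week 20. It does not close the gap, because a possible route to follow-up is not a commitment to it.

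A second reply is that the detail may sit in material not shown, such as the self-harm protocol that the article cites or the e-helper training, whose syllabus has headings on high-risk situations and on post-assessments. A journal article does leave such procedures out. Here, though, the article states the window, and the stated window does not match its own schedule. If the fuller material already covers week 20, bringing this sentence into line costs almost nothing.

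A third reply is that the staffing remark is speculative and that no arm-specific gap is shown. Both are fair. The safety text speaks of participants in general, and e-helpers may also be community health workers. Naming both arms is still sensible, because the article describes routine e-helper contact for the intervention group only.

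**Conclusion.** The point holds. As written, an item-9 score of 2 or above has a weaker stated response at week 20 than at week 8: follow-up of the participant is promised at week 8 and not at week 20, which is the last planned assessment. The gap covers one scheduled PHQ-9 administration, due in both arms. The number of people affected is unknown, because the article reports no item-9 frequency.

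This rests on reading the named window literally and on taking the untimed sentences at their most generous. It does not assume that follow-up would fail to happen in practice. It is a participant-safety point that should be corrected. No estimand, analysis or primary result is touched. Confidence is moderate, because an operational document not shown may already cover week 20.

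**What to change.** Extend the sentence in Ethical and safety considerations so that item-9 referral and follow-up apply at every PHQ-9 administration after enrolment, naming the week-20 follow-up and both arms explicitly. State that e-helper or supervisor cover continues until the last week-20 assessment has been completed; because e-helping is run as a student practicum, it is safer to write this down than to assume it. The clinical content of the rule, such as what follow-up consists of and who carries it out, is for the investigator and the ethics committee.

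The cost is one longer sentence and an alert setting in the app, using an item already collected. The price is a small additional referral workload and the staffing needed to keep cover through week 20.
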